### Recruitment

Given the large number of surgical interventions performed under general anaesthesia at the study centres involved each day and only little restrictive inclusion and exclusion criteria, insufficient numbers of potential study participants are not to be expected. Because the additional burden on the participants while participating in the study is deemed to be manageable, a high recruitment rate can be assumed. We do not expect substantial problems with protocol adherence due to the short duration of the intervention.

Randomization takes place automatically through computer-aided generation of random numbers, which are translated into a randomization decision and will be triggered online by the respective investigator on the day of the intervention at the earliest, so that a concealed allocation to the interventions is ensured (allocation concealment). The randomization result will be communicated non-verbally to the anaesthetist and the nursing staff involved via a display on the tablet monitor to ensure that the patient remains blinded.

The generation of the allocation sequences and the allocation to the individual intervention arms takes place via an IT-based system (OpenClinica, Waltham, MA, USA) coordinated by the Center for Clinical Studies of the German Association of Anaesthesiology and Intensive Care (DGAI).

If the anaesthetist in charge of the intervention decides not to leave the choice of the intubation instrument to chance for medical reasons before the induction of anaesthesia and prior to randomization, the participation in the trial for this patient and the case will be considered a “screening failure”. If such a decision (deviating from the randomization result) is made after the patient has been randomized but before the start of the first intubation attempt, the first intubation attempt will be.considered to have failed. These cases will be reported separately in the study flow chart. The remainder of intervention as per protocol remains unaffected. After a first intubation attempt with the randomized laryngoscopy device, the anaesthetist performing the procedure is free to change the instrument at his/her own discretion. The required intubation attempts and the time to successful intubation are recorded as described above.

In addition, the study protocol does not make any specifications for handling possible complications in securing the airway. The physician carrying out the intervention always has unrestricted authority to make medical decisions to prevent harm to the patient without affecting the patient’s participation in the study.

### Blinding

Patients and data analysts will be blinded regarding the allocation of interventions. The randomization result will be communicated to the care providers non-verbally in such a way that the patient will not take note. Before data will be evaluated, the identifying variable names will be made unrecognizable. For the study observers and the personnel carrying out the intervention, blinding is not possible due to the nature of the study. In the follow-up period two hours after the end of anaesthesia, the survey of the outcomes should be carried out, if possible, by an observer who was not involved in the intervention, to encourage blinding of the investigator here as well. It will be documented whether blinding could be facilitated at this point.

Un-blinding of the patient is intended only in cases when an unexpected difficult airway situation occurred, and the patient needs to have an anaesthesia problem card issued for them. However, even in such cases, blinding can usually be kept up until after the last study visit.

### Biometry

The required socio-demographic data as well as data on the surgical procedure will be assessed by chart review beforehand and will be included in the study documentation as source data. All other necessary data are determined and recorded by the investigator or observer during the intervention in real time. The questionnaires on teamwork and task load will be filled out by the care providers as soon as the ongoing procedures allow for. The principal investigator at each study site will be responsible for the timely documentation in the electronic case report form (eCRF) and the proper documentation and storage of source data according to applicable local laws.

All data relevant to the trial will eventually be entered into an eCRF and stored in an electronic database provided by OpenClinica LLC (Waltham, MA, USA). Hosting of the database in accordance with German and EU laws will be ensured by Docs In Clouds Telecare GmbH (Aachen, Germany).

Data collection forms can be requested from the authors.

### Statistical analysis

The primary outcome is the rate of successful intubations at first attempt as a fraction of dichotomous events. In a first analysis step we test the hypothesis, that neither video assisted laryngoscopy with a Macintosh-shaped blade (M-VAL) nor video assisted laryngoscopy with a hyper-angulated blade (H-VAL) are inferior to conventional direct laryngoscopy (CDL) with regard to the primary outcome. In terms of the statistics, this corresponds to testing the Null hypothesis that at least one of the interventions M-VAL or H-VAL is inferior to CDL. Both Null hypotheses will be tested for separately. The overall type-I error will be set to 5%. Thus, both Null hypotheses will be tested on a local significance level of 0.025 using a one-sided Z-test with unpooled variance. Non-inferiority is defined as described in subsection “sample size”.

Only if both Null hypotheses can be rejected will there be a second analysis step where the single interventions M-VAL and H-VAL will be tested pairwise for superiority using a two-sided Z-test with unpooled variance. As we apply the principle of fixed sequence hierarchical testing, this analysis can be performed at a local significance level of 0.05 to meet the family-wise error rate of 0.05.

A planned interim analysis will be conducted after 200 randomized interventions. This will first and foremost happen to review feasibility and data quality before expanding to additional study sites. We do not foresee any substantial safety concerns in this trial which would need to be assessed at this stage.

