### Choice of comparators

In this study, three different modalities of laryngoscopy for endotracheal intubation will be compared (s. Fig. 1): 1. conventional, direct laryngoscopy using a Macintosh blade. This procedure is considered the gold standard and is routinely used in the peri-operative setting as well as in intensive care and emergency medicine. 2. use of VAL with a Macintosh-shaped blade. By positioning the camera at the tip of the blade, the field of view onto the glottic plane is improved, as there is no need to establish a direct line of sight from the outside to the tracheal inlet (as is the case with conventional laryngoscopy). 3. use of VAL with a hyper-angulated blade. This shape of laryngoscope blade cannot be used in conventional, direct laryngoscopy because the strong curvature renders a direct line of view from the outside impossible due to the geometry of the instrument. So far, hyper-angulated blades are often used as a backup instrument when a view of the glottic plane cannot be achieved with the Macintosh blade due to anatomic abnormalities, even with a video-assisted laryngoscope. This often enables endotracheal intubation in patients who could otherwise not be intubated through conventional laryngoscopy. At the same time, however, it is conceivable that the rather extreme curvature of the blade may prove disadvantageous in individual cases compared with less curved blade variants. This may be because insertion of the tube is difficult due to the curvature of the blade and indirect vision, or because fluids like mucus or blood make it impossible to see through the video-optical system.

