### Sample size

The estimation of the appropriate sample size is based on the corresponding Null hypotheses of the primary hypothesis, i.e. the assumption that VAL is inferior to conventional laryngoscopy in terms of first-attempt success rate, irrespective of the kind of blade in use. From clinical experience and previously published data, we assume an a-priori success rate of 90% across all groups. A clinically relevant difference between groups in this context is suggested at 5%, as is the accepted overall type-I error. Given that both Null hypotheses will be tested separately, the type-I error limit in each case is 2.5%. The desired statistical power is set to 90%. The Null hypotheses will be tested for non-inferiority using a one-sided Z test with unpooled variance. Based on these assumptions, the required sample size amounts to 3 * 824 = 2526 participants.

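### Step 1 requires both blades to pass, but alpha is halved as if either could pass alone, and the 90% power holds only per comparison

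*Protocol article*

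**What the plan says.** All of this stands in the protocol article.

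- **Null hypothesis (Statistical analysis).** The step-1 hypothesis is that neither video blade is inferior to direct laryngoscopy, and "this corresponds to testing the Null hypothesis that at least one of the interventions M-VAL or H-VAL is inferior to CDL".
- **Gate (Statistical analysis).** "Only if both Null hypotheses can be rejected will there be a second analysis step", in which the blades are compared for superiority at two-sided 0.05.
- **Alpha (Sample size).** "A clinically relevant difference between groups in this context is suggested at 5%, as is the accepted overall type-I error". Then: "Given that both Null hypotheses will be tested separately, the type-I error limit in each case is 2.5" percent. Statistical analysis repeats this as a local one-sided level of 0.025.
- **Power (Sample size).** "The desired statistical power is set to 90" percent, without saying whether this is per comparison or for both together. The planning assumption is "we assume an a-priori success rate of 90% across all groups".
- **A different step 1 (Hypothesis and experimental approach; Design).** There the two video arms are first pooled and compared with control, and the individual arms are compared only afterwards.

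**The concern.** The hypothesis and gate describe one decision rule, and the alpha split serves another. If the null is that at least one blade is inferior, it falls only when both tests reject. A false rejection then requires the truly inferior blade to pass its own test, so the overall step-1 error cannot exceed the level of a single test. Halving is needed only when either blade may be claimed alone.

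What a both-must-win rule costs is power, because two tests must succeed together. A sample size that gives 90% for one comparison gives less for both. At stake are the stated chance of a positive primary result and of reaching step 2, and whether the article describes its own error control correctly.

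**Working it through.** **Inputs.** From Sample size: success 0.90 in all arms, margin 0.05, one-sided 0.025 per test, power 90%, unpooled Z test. From Design: 1:1:1 allocation. The two test statistics share the control arm, so their correlation is about 0.5.

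**1. The plan's own figure.** For one comparison:

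n = (1.960 + 1.282)² × 2 × 0.90 × 0.10 / 0.05² = 756.5, so 757 per arm (2271 in total).

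The article prints 3 × 824 = 2526, but 3 × 824 = 2472 and 2526 = 3 × 842. Neither 824 nor 842 follows from the stated inputs. A 10% loss allowance on 757 gives 842, but the article states no dropout, so that reading is an assumption. Power is shown below for all three sizes.

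**2. Power for one test and for both.** Let c = 0.05 / √(0.18/n) − z, with z = 1.960 (one-sided 0.025) or 1.645 (one-sided 0.05). Single power is Φ(c). Joint power is the bivariate normal probability Φ₂(c, c; 0.5).

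| n per arm | c at 0.025 | one test at 0.025 | both at 0.025 | both at 0.05 |
|---|---|---|---|---|
| 757 | 1.283 | 90.0% | 83.3% | 90.4% |
| 824 | 1.423 | 92.3% | 86.8% | 92.7% |
| 842 | 1.460 | 92.8% | 87.6% | 93.2% |

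Simulation at 842 per arm and 0.025 per test gives 87.2% for both. Joint power of 90% needs about 901 per arm at one-sided 0.025, or about 748 at one-sided 0.05.

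**3. Type-I error of step 1 at 0.025 per test.**

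- One blade on the margin, the other equal to control: 2.5%. This is essentially the maximum.
- Both blades on the margin: 0.46% (normal approximation).
- If either blade could be claimed alone, both on the margin: 2 × 0.025 − 0.0046 = 4.5%. This is the case the split fits.

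**4. Error of the whole two-step procedure.** Simulated at 842 per arm with equal arms, step 2 at two-sided 0.05:

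| Step 2 tests | arms at 90% | arms at 95% |
|---|---|---|
| Macintosh-shaped v hyperangulated video blade only | 3.0% | 4.7% |
| all three pairs, unadjusted | 6.6% | 11.6% |

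**The case against.** **Step 1 is conservative.** The 5% is a ceiling that step 1 does not breach, and one-sided 0.025 is an ordinary level for a non-inferiority test. This stands: no step-1 inference is invalid. What fails is the reason given for the level.

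**The 90% may be meant per comparison.** The article does not say it is joint, and read per comparison it is met at all three sizes. This also stands, but then the power for the hypothesis the article calls primary is given nowhere.

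**Under pooling the issue disappears.** If step 1 is the pooled comparison, there is one test and no joint-power question. That is correct, and it is why the step-1 rule has to be settled first.

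**Requiring both blades is a legitimate choice.** The declared aim is to judge video laryngoscopy as a method, whatever the blade. This stands; the gate is not an error.

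Three stronger readings are tempting, and the document does not support them.

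- *The overall type-I error is 2.5%.* This is true of step 1 only. Step 2 at 0.05 raises the error of the whole procedure, and above 5% if all three pairs are tested without adjustment.
- *The real power is 83%.* That takes 757 as the number left after a 10% loss, which the article does not state. The primary outcome is observed in real time, and under Recruitment a departure from the allocated device before the first attempt counts as a failure, not as missing.
- *The gate buries a real benefit of the Macintosh-shaped video blade.* With assumed rates of 90% for control, 94% for that blade and 88% for the hyperangulated blade, the chance of showing the Macintosh-shaped video blade superior to control is 47% under the gate and 86% on its own branch. With the hyperangulated blade at 90% it is 82% v 86%. The rates are not in the article, which assumes 90% throughout. Choice of comparators says only that "it is conceivable that the rather extreme curvature of the blade may prove disadvantageous in individual cases", which does not imply a lower average rate.

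**Conclusion.** The mismatch is real and is confined to step 1. The rule is both-must-win, the alpha is set for either-may-win, and the 90% is a per-comparison figure. The step-1 error is at most about 2.5% where the text budgets 5%. Joint power falls short of 90% by 3.2 points at 824 and 2.4 points at 842 evaluable per arm. At 757 the shortfall is 6.7 points, if that were the number analysed.

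These figures assume 90% true success in all arms, a shared control with equal allocation, and the both-must-win rule of Statistical analysis rather than the pooled comparison. The point should be fixed, but it does not invalidate the trial: the step-1 error is conservative, the shortfall at the printed sizes is small, and the remedy is wording.

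**What to change.** 1. **State one step-1 rule.** Reconcile the both-must-win test in Statistical analysis with the pooled comparison in Hypothesis and experimental approach and in Design.
2. **If both blades are required, match alpha and power to that rule** in one of two ways:
   - Keep one-sided 0.025 per test as a deliberately chosen level, drop the two-nulls justification, and restate power as about 87–88% joint and 92–93% per comparison.
   - Test each at one-sided 0.05, where the current size gives about 93% joint power at a step-1 error of 5%.
3. **Do not print 2.5% as the error of the full procedure.** State which pairs step 2 tests. If it tests all three, an adjustment is needed.
4. **Optional: separate branches.** Each blade could claim non-inferiority at one-sided 0.025 and then go to its own superiority test against control at the same level. By Bonferroni the two branches stay within 5%. The comparison between the video blades must then wait until both superiority tests have succeeded, or be left exploratory. Run at 0.05 once both blades are merely non-inferior, it takes the total to about 6.6% (arms at 90%) to 8.3% (arms at 95%). This option changes the claim to a blade-specific one and is a design choice, not a correction.

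The cost is wording in Sample size and Statistical analysis, with no extra patients. Under the first alternative in item 2 the stated power becomes slightly less favourable. The rule must be fixed before unblinding, since choosing it afterwards would undermine the primary claim.

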## Methods and design

### Design

This is a randomized controlled multi-centre study with a three-arm parallel study design (s. Fig. 2). The primary endpoint is the successful placement of the endo- tracheal tube at first attempt (success at first attempt) as a dichotomous feature. The patients included in the study will be evenly distributed across the three study arms (1:1:1). The underlying approach is the premise of non-inferiority of the experimental interventions compared to the established standard procedure.

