AgeGenderHeight and weightASA classificationMallampati scoreupper lip bite test (ULBT) classification

Where applicable, these can be obtained from the patient’s chart.

Care provider-related data to be collected are:

Job experience (years; anaesthetist only)

The observable outcomes will in part be captured using the Work Observation Method By Activity Timing (WOMBAT) software (WOMBAT 3.0, 2020) [28].

Schedule of activities.

See Table. 1

**Table 1 Tab1:** Schedule of activities

	Screening	randomization	intervention	post-intervention	follow-up
	up to 14 days prior to intervention	day 0 briefly before intervention	day 0	day 0 immediately after intervention	day 0 2 h (± 30 min) after extubation
visit	V1	V2	V3	V4	V5
inclusion criteria	X				
exclusion criteria	X				
informed consent	X				
registration	X				
sociodemographics, medical history	X				
acute medical concerns by responsible anaesthetist preventing randomization		X			
randomization		X			
experience of *anaesthetist*			X		
upper lip bite test, Mallampati score	X		(X)^a^		
pre-oxygenation (> 80% etO_2_), relaxation (TOF = 0)			X		
intubation (incl. number of attempts and time to intubation)			X		
Cormack-Lehane grade			X		
switch of device or provider			X		
vital signs			X		
injuries			X		
Mayo High Performance Teamwork scale				X	
NASA-TLX				X	
sore throat, coughing, hoarseness					X

^a^ if these parameters cannot be obtained from the patient’s chart, they will be obtained by the observer prior to the intervention

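### The primary non-inferiority test is fixed as unadjusted although baseline predictors and centre are already recorded; it is valid but gives away a modest amount of precision

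*Protocol article*

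**What the plan says.** The test is fixed in two places in the protocol article, and they agree. Under Sample size the null hypotheses are "tested for non-inferiority using a one-sided Z test with unpooled variance". Under Statistical analysis they are "tested on a local significance level of 0.025 using a one-sided Z-test with unpooled variance". Neither section names a covariate or a centre term.

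The design inputs are under Sample size:
- Success rate: "we assume an a-priori success rate of 90% across all groups".
- Margin and overall error: "A clinically relevant difference between groups in this context is suggested at 5%, as is the accepted overall type-I error".
- Per hypothesis, "the type-I error limit in each case is 2.5" percent.
- Power: "The desired statistical power is set to 90" percent, without saying whether this is per comparison or for both comparisons together.

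Under Statistical analysis, the second step opens only if both null hypotheses are rejected.

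The Outcomes section lists age, gender, height, weight, ASA class, Mallampati score, upper lip bite test (ULBT) and the anaesthetist's years of experience as data to be collected. The Design section calls the trial multi-centre, and Setting places sites in Germany, Austria and Switzerland. The account of randomisation under Recruitment mentions no stratification.

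In Table 1, randomisation is at V2 and Mallampati and ULBT are at V1. If those scores are not in the chart, the footnote says "they will be obtained by the observer prior to the intervention", which is V3. Experience of the anaesthetist is also entered at V3.

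**The concern.** For a binary outcome, using baseline predictors through standardisation leaves the estimand and the margin unchanged and narrows the interval. Here the data are already being collected. Operators range upward from one year of training, laryngoscope models are not restricted and several sites take part, so part of the variation in first-pass success is plausibly explained by what is recorded. Because the protocol itself names the primary test, an analysis plan could not make an adjusted estimate primary without contradicting it.

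Precision matters most for the joint claim: the second step is reached only if both video arms pass, and that is harder than passing one comparison.

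The timing in Table 1 is a lesser matter. A Mallampati or ULBT score graded at V3 may be graded by an observer who already knows the arm, since Blinding says observers cannot be blinded. The operator is likewise documented only after allocation has been shown. This matters only if these variables are used for adjustment or subgroups.

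**Working it through.** **Inputs from the article.** Success rate 0.90 in all arms, margin 0.05, one-sided level 0.025, power 90%, allocation 1:1:1, unpooled variance.

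**The plan's own figure.** n per arm = 2 × 0.90 × 0.10 × (1.960 + 1.282)² / 0.05² = 0.18 × 10.507 / 0.0025 = 756.5, so 757 per arm and 2271 in total. The article states 3 × 824 = 2526. That product is 2472, and 2526 / 3 = 842. Neither 824 nor 842 follows from the stated inputs. 757 / 0.90 rounds up to 842, which would fit a 10% loss allowance, but none is stated. I use 842 as the main case and also show 824 and 757.

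**Unadjusted power.** For a true difference of zero, SE = √(0.18 / n) and c = 0.05 / SE − 1.960. Power per comparison is Φ(c). The two comparisons share the control arm, so their correlation is (0.09/n) / (0.18/n) = 0.5. Joint power is the bivariate normal probability that both statistics fall below c.

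| n per arm | SE | c | Per comparison | Both nulls |
|---|---|---|---|---|
| 757 | 0.01542 | 1.283 | 90.0% | 83.3% |
| 824 | 0.01478 | 1.423 | 92.3% | 86.8% |
| 842 | 0.01462 | 1.460 | 92.8% | 87.6% |

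About 901 per arm (2702 in total) would give 90% joint power without adjustment.

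**With adjustment.** If covariates explain a fraction R² of outcome variance, SE becomes √(0.18 × (1 − R²) / n), equivalent to an effective n of n / (1 − R²). R² is an assumption. At 842 per arm:

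| Assumed R² | Effective n | 1.96 × SE (points) | Per comparison | Both nulls |
|---|---|---|---|---|
| 0 | 842 | 2.87 | 92.8% | 87.6% |
| 3% | 868 | 2.82 | 93.5% | 88.7% |
| 5% | 886 | 2.79 | 93.9% | 89.5% |
| 10% | 936 | 2.72 | 95.0% | 91.2% |

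At 824 per arm, R² of 5% and 10% gives 93.5% and 94.6% per comparison, and 88.7% and 90.5% jointly. At 757, R² of 3%, 5% and 10% gives 84.6%, 85.4% and 87.6% jointly.

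**R² needed for 90% joint power.** About 6.5% at 842, 8.5% at 824 and 16% at 757.

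**How demanding that is.** Simulating a single normally distributed prognostic score with 90% overall success, an R² of about 2%, 5% and 9% corresponds to an AUC of about 0.64, 0.70 and 0.75. The documents do not say where the recorded variables would fall.

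**The case against.** The strongest reply is that nothing here is an error. A crude two-proportion test is valid under randomisation, estimates the risk difference on which the margin is set, and is the test assumed in the sample size. Its type-I error already allows for chance imbalance. All of that stands, and the point is therefore one of efficiency. Supportive adjusted analyses may well be in an analysis plan that is not shown, but the choice of primary test is made in this article.

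Several stronger readings are tempting and are not supported:

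- *The trial falls short of its stated power.* This holds only if the 90% means power to reject both nulls. Per comparison it is met at 757, 824 and 842.
- *The recorded predictors are strong.* No figure in the article supports this. The Setting section excludes patients needing fibreoptic intubation, those scheduled for bariatric surgery and those judged unsafe to randomise, and it sets a minimum operator experience. These limits may narrow the spread of the predictors.
- *Table 1 timing biases the primary result.* The planned test uses none of these variables. V3 is only a fallback for the airway scores, and years of experience is a fixed fact about a given operator. It could depend on the arm only if the operator changed after allocation.

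Adjustment also has drawbacks. With about 10% failures and an unstated number of centres, some small centres may have no failures, and Mallampati or ULBT may be missing. Both need a stated rule.

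**Conclusion.** The point holds as a worthwhile, inexpensive improvement to a stated method. At 842 per arm, an assumed R² of 3% to 10% adds 0.7 to 2.2 percentage points of power per comparison (93.5 − 92.8; 95.0 − 92.8) and 1.1 to 3.6 points jointly (88.7 − 87.6; 91.2 − 87.6). Adjustment does not guarantee 90% joint power: at 842 it needs an R² of about 6.5%. The figures rest on 90% success in every arm, no true difference, a correlation of 0.5 from the shared control, and the assumed R². The Table 1 timing is a minor accompanying matter that becomes relevant once the covariates are used.

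**What to change.** 1. In Statistical analysis, make the primary estimate for each video arm against direct laryngoscopy a marginal risk difference. Obtain it by standardisation after logistic regression on arm, Mallampati, ULBT, BMI (from recorded height and weight), years of experience and centre, with a robust standard error. Compare the one-sided 97.5% bound with the unchanged 5-point margin. A conditional odds ratio should not replace it, because it would not match the margin.
2. State in advance how small centres are pooled, and use one simple imputation rule for missing covariates, the same in every arm and blind to outcome.
3. Keep the crude Z-test as the supportive analysis.
4. In Table 1, move any fallback Mallampati or ULBT to V2 and name the intended operator there, before randomisation is triggered.
5. Under Sample size, say whether 90% is per comparison or joint, and reconcile 824 with 2526.

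The cost is analysis-plan text, a few lines of code, a changed order of eCRF entries and slightly more analytic complexity. No extra patients or new variables are needed. Because the test is in the protocol, the change needs an amendment, which Ethics approval says goes to the committee. The analysis change must be settled before unblinded data are seen, and the Table 1 change helps only patients not yet randomised.

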**Fig. 1 Fig1:**
[figure not shown]
Examples of different laryngoscopes to be used in each of the three study arms (from left to right): conventional laryngoscope with Macintosh blade, video-assisted laryngoscope with Macintosh-shaped blade, video-assisted laryngoscope with hyper-angulated blade

After testing the non-inferiority of the experimental intervention (VAL as an overall procedure) compared with the control group, pairwise comparisons between the study arms will also be of interest. If this step of the hierarchical analysis plan can be reached, testing for superiority between groups will be possible. Furthermore, the question of whether the primary use of a hyper-angulated blade may be useful can be explored. In this scenario, for example, the hyper-angulated blade would not be inferior in the general setting, but would possibly make a second intubation attempt, or a change of the device used, unnecessary in the case of an unexpectedly difficult airway, since the “rescue device” has already been used to begin with.

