**Fig. 2 Fig2:**
[figure not shown]
Flow diagram

The “conventional laryngoscopy” study arm serves as a control group in this experimental setup. The two study arms using VAL will initially be combined at the first stage of the analysis to show that the method “VAL” is non-inferior to the established gold standard regardless of the blades used. If this first analysis can prove non-inferiority, the three individual groups will also be compared against each other.

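### The step-2 superiority tests are not a fixed sequence: if the three arms are compared pairwise at 0.05, the stated 5% family-wise error becomes about 6.6% at the assumed 90% success rate, with a ceiling of about 12%

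*Protocol article*

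**What the plan says.** The Statistical analysis section sets two steps. In step 1, M-VAL and H-VAL are each tested for non-inferiority to CDL: "both Null hypotheses will be tested on a local significance level of 0.025 using a one-sided Z-test with unpooled variance". The gate is explicit: "Only if both Null hypotheses can be rejected will there be a second analysis step". In step 2, "the single interventions M-VAL and H-VAL will be tested pairwise for superiority using a two-sided Z-test with unpooled variance". The error claim follows: "this analysis can be performed at a local significance level of 0.05 to meet the family-wise error rate of 0.05". The ground given for it is that the tests form a fixed hierarchical sequence.

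Two other places describe what follows non-inferiority. Choice of comparators (text after Fig. 1) says that "pairwise comparisons between the study arms will also be of interest" and goes on to superiority testing between groups. Design (text after Fig. 2) says that "the three individual groups will also be compared against each other". None of the three places gives an order, a stopping rule or an adjustment among these comparisons.

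The Abstract presents superiority of one of the interventions as part of the pre-defined hierarchy. The Discussion says that superiority of VAL could be proved under the chosen design.

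**The concern.** A fixed sequence passes the full 0.05 from one hypothesis to the next single hypothesis. It does not pass 0.05 to several hypotheses at once. The gate controls entry to step 2. Once step 2 is open, two or three unordered tests at 0.05 form a family of their own, and the argument given does not cover that family.

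The number of tests is also unsettled. The step-2 sentence can be read as one test (M-VAL vs H-VAL), two (each VAL arm vs CDL) or three (all pairs). A superiority finding would be reported as confirmatory under a 5% guarantee that holds on only one of these readings, and the undefined test set leaves room to choose comparisons after the data are seen.

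**Working it through.** **Inputs.** Local level 0.05 two-sided in step 2; one-sided 0.025 for each non-inferiority test; both must succeed; unpooled Z-tests (Statistical analysis). Margin 5 percentage points and a common success rate: "we assume an a-priori success rate of 90% across all groups" (Sample size). Allocation 1:1:1 (Design). The arm size is an assumption: Sample size prints 3 × 824 = 2526, but 3 × 824 = 2472 and 2526/3 = 842. I use 842 and show the sensitivity below.

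**The plan's own figure.** A single M-VAL vs H-VAL test at 0.05 has an error of 5.0% before the gate. With the gate it is 3.0%, 4.8% and 5.1% at 90%, 95% and 97% success. So the stated 0.05 is reproduced, to within the accuracy of the Z-test, if step 2 holds exactly one test.

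**Several tests, ignoring the gate, all arms equal.**
- Three pairs, if they were independent: 1 − 0.95³ = 14.3%.
- Three pairs in equal arms, which are correlated: the chance that a studentized range of three means exceeds 1.96 × √2 = 2.77 is 12.2%. This is the ceiling.
- Two tests against CDL: 9.1% by simulation.

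**With the gate.** Binomial simulation of the whole procedure, 2,000,000 trials per setting, 842 per arm, all arms equal:

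| True success | Gate passed | Three pairs | Two tests vs CDL |
|---|---|---|---|
| 85% | 71% | 5.5% | 4.6% |
| 90% | 87% | 6.6% | 4.6% |
| 93% | 96% | 8.6% | 5.5% |
| 95% | 99% | 11.6% | 8.5% |
| 97% | 100% | 12.3% | 9.2% |

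At 90% success the three-pair figure is 6.5% with 824 per arm and 6.2% with 757, so the choice of arm size matters little.

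**Why the gate helps at 90% and not at 95%.** At 90%, the standard error of a difference is √(2 × 0.9 × 0.1/842) = 0.0146. CDL is significantly better than a VAL arm when the observed difference (VAL minus CDL) is below −1.96 × 0.0146 = −0.029. Non-inferiority requires it to be above −0.05 + 0.029 = −0.021. The two cannot both happen, so the gate removes every false finding in favour of CDL. At 95%, the standard error is √(2 × 0.95 × 0.05/842) = 0.0106. The limits become −0.021 for significance and −0.029 for non-inferiority, so a difference between them passes the gate and is also significant. The protection is a by-product of the margin and the success rate, not of the testing principle cited.

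**Direction of the false findings, with the gate.** Either VAL arm falsely better than CDL: 4.6%, 4.6% and 4.7% at 90%, 95% and 97%. CDL falsely better than a VAL arm: 0%, 3.9% and 4.5%. M-VAL vs H-VAL: 3.0%, 4.8% and 5.1%. These events overlap, so they do not add up to the totals above.

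**The case against.** The strongest defence is textual. The Statistical analysis section is the operative text; it names only M-VAL and H-VAL and speaks of one analysis at one local level. Read as a single M-VAL vs H-VAL contrast after a step 1 in which both nulls must be rejected, it is a valid fixed sequence and the 0.05 claim is true. The other two places are overview text and set no level. This shows that the inflation depends on the reading. It does not rescue the plan, because that reading conflicts with the Design section and leaves no test of VAL against CDL, which the Abstract and Discussion rely on. An unseen analysis plan may fix the order, but the 5% claim is printed here without condition.

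Three stronger conclusions are tempting, and the documents do not support them.
- A reader might infer that the trial as planned runs a 12% error. That figure needs three tests and true success of about 95% or more in every arm. At the assumed 90% it is 6.6%, and with two tests it is below 5%.
- A reader might infer that a claim of VAL beating CDL carries more than twice the stated error. It does not: two upper tails of 0.025 bound that error at 5% by Bonferroni, and simulation gives 4.6% to 4.7%. The excess comes from adding false CDL superiority and M-VAL vs H-VAL findings.
- A reader might infer that the primary result is compromised. Step 1 requires both nulls to be rejected, so it adds no inflation.

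**Conclusion.** The point stands as a wrong or undefined statement about step 2. If all three arms are compared with each other, unordered and unadjusted, the family-wise error exceeds 0.05 at every success rate tried from 85% to 98%: about 6.6% at the protocol's 90%, with a ceiling of about 12%. With two tests against CDL it is 4.6% at 90% and up to about 9%. Only the single M-VAL vs H-VAL test meets the claim, and it contradicts other parts of the protocol.

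The figures assume equal true success in all arms, 842 per arm, and the gate as two separate non-inferiority tests, as the Statistical analysis section has it. At the assumed success rate the excess is modest. But the control is stated without condition, and the Discussion itself expects high success rates, which is where the gate gives least protection. The non-inferiority conclusion is not affected.

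**What to change.** Name the step-2 comparisons (M-VAL vs CDL, H-VAL vs CDL, M-VAL vs H-VAL, or a stated subset) and make Choice of comparators, Design and Statistical analysis agree. Then control them in one of three ways, fixed before any unblinded analysis:

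1. A pre-stated order, each test at 0.05 only after the previous one succeeds. This is closest to the plan's own principle and caps the error at 5%. The first test loses no power; later ones depend on the earlier ones.
2. Holm over the named tests. Its first step for three pairs, at 0.05/3 = 0.0167, gives a family-wise error of 4.5% without the gate and 2.2% with it at 90% success.
3. A 2-df chi-square test of the three arms at 0.05 before the pairs. With exactly three arms, any two pairwise equalities imply the third, so this is a closed procedure and each pair keeps 0.05. The family-wise error with the gate is 2.4%, 4.3% and 4.9% at 90%, 95% and 97%.

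No patients or data are added. The cost is superiority power. For 90% vs 95%, testing at 0.0167 instead of 0.05 lowers power from 97.4% to 93.4%. For smaller differences the loss is larger. With the three-arm test in front, power for M-VAL vs CDL falls from 86% to 77% at true rates of 90/94/92% (CDL/M-VAL/H-VAL), and from 58% to 50% at 90/93/90%. If only the M-VAL vs H-VAL test is meant, no adjustment is needed, but the statements that superiority of VAL over CDL can be tested must then be withdrawn.
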